### Recruitment

Approximately 24 hepatology clinicians will be recruited for the clinician-level randomized crossover simulation. This sample size was selected pragmatically to provide sufficient clinician-level feedback on usability, cognitive workload, trust, and workflow integration while remaining feasible for a pilot implementation study. Eligible clinicians will include hepatologists, advanced practice clinicians, and hepatology trainees with clinical experience managing patients with PBC. Participants will be recruited from hepatology clinics affiliated with academic medical centers.

### Randomization

Randomization will apply only to the implementation phase of the study during the clinician-level crossover simulation. Clinicians will be randomly assigned in a 1:1 ratio to 1 of 2 sequences: usual care followed by CDS-assisted care or CDS-assisted care followed by usual care. A computer-generated randomization schedule will be used to balance allocation between sequences and minimize allocation bias. The simulation will use standardized, deidentified cases rather than live clinical encounters.

To minimize learning and carryover effects, the 2 simulation periods will use distinct, nonoverlapping standardized cases matched in clinical complexity. A 1-week washout period will separate the 2 conditions, and case order will be varied within each period where feasible. Primary comparisons will be conducted within clinicians, allowing each participant to serve as their own control (Figure 2).

**Figure 2. F2:**
[figure not shown]
AIm-PBC clinician-level crossover randomized controlled trial pilot design. EHR: electronic health record; FTE: full-time equivalent. DO: doctor of osteopathic medicine; MD: doctor of medicine; NP: nurse practitioner; PA: physician assistant.

### Data Collection

Retrospective data will be sourced from institutional EHRs and data warehouses, capturing historical laboratory values, elastography reports, and clinical outcomes relevant to PBC. Prospective data collection will be conducted in outpatient hepatology clinics using secure, HIPAA (Health Insurance Portability and Accountability Act)-compliant platforms such as REDCap for PROs. These outcomes will include validated instruments such as the WI-NRS, administered twice daily to capture circadian variation in pruritus, and the PBC-40 questionnaire, administered monthly to assess quality of life domains.

Biochemical data, including ALP, bilirubin, aminotransferases, albumin, and platelet count, will be collected at monthly intervals to provide high-resolution longitudinal trajectories. LSM and SSM values will be obtained at baseline and during scheduled follow-up visits, with probe frequency and stiffness values recorded in kilopascals to ensure standardization. Clinical outcomes such as time to variceal development, ascites, and hepatic encephalopathy will be tracked over a 24-month observation period.

All data will be deidentified prior to analysis and stored in secure environments that comply with institutional and federal privacy regulations. Quality control procedures will include automated range checks for laboratory values, standardized reporting templates for elastography, and audit trails for PRO completion. Missing data will be addressed using multiple imputation techniques to minimize bias and preserve statistical power. Data integration will occur through structured pipelines that normalize heterogeneous inputs for use in machine learning models, ensuring consistency across biochemical, imaging, and symptom domains.

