### Eligibility Criteria

Adults aged 18 years or older with a confirmed diagnosis of PBC according to American Association for the Study of Liver Diseases criteria (ie, defined as elevated ALP of ≥1.5 times the upper limit of normal in combination with a positive antimitochondrial antibody or disease-specific antinuclear antibodies such as sp100 or gp210) [2]. For individuals who are seronegative, histological confirmation through liver biopsy will be mandatory. All participants must have been receiving standard therapeutic dosing of ursodeoxycholic acid for a minimum of 3 months prior to enrollment, defined as 13 to 15 mg per kilogram of body weight per day administered in 2 or 3 divided doses [2]. Patients who are on second-line therapies, including farnesoid X receptor agonists or peroxisome proliferator–activated receptor agonists, will also be eligible, and therapy class will be recorded as a covariate. Additionally, baseline elastography data, including LSM and SSM, must be available within 6 months of enrollment.

Individuals will be excluded if they have previously undergone liver transplantation or are currently listed for transplantation or if they present with decompensated cirrhosis at baseline, defined as Child-Pugh class B or C [16]. Other exclusion criteria include active malignancy, uncontrolled systemic illness, pregnancy, or inability to provide informed consent. Patients with significant alcohol consumption within 6 months of enrollment (ie, more than 20 grams per day for female individuals or more than 30 grams per day for male individuals or an Alcohol Use Disorders Identification Test–Consumption score of 4 or higher) [17] will not be eligible. Additional exclusions are coexisting chronic liver diseases such as chronic viral hepatitis, hemochromatosis, Wilson disease, or alpha-1 antitrypsin deficiency, as well as active or suspected drug-induced liver injury within the prior 6 months, including drug-induced autoimmune hepatitis (AIH). Any condition deemed by the investigators to compromise participant safety or data integrity will also result in exclusion. A summary of inclusion and exclusion criteria is provided in Textbox 1.

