### Participant Timeline

Participants will enter the study and begin with baseline assessments, which include collection of demographic information, medical history, and initial laboratory values, as well as elastography measurements for liver and spleen stiffness. At this visit, participants will also be enrolled in the PRO system, with instructions for completing the WI-NRS and the PBC-40 questionnaires. These assessments will continue throughout the observation period to capture longitudinal symptom trajectories. The schedule of enrollment, interventions, and assessments is provided in Checklist 1.

Biochemical data will be collected at monthly intervals for the duration of the study, ensuring high-resolution monitoring of disease activity. Elastography will be repeated at predefined intervals, typically every 6 to 12 months or as clinically indicated, to track changes in liver and spleen stiffness over time. Clinical outcomes such as the development of varices, ascites, or hepatic encephalopathy will be monitored continuously through routine clinical care and documented in the study database.

For participants involved in the implementation phase, the timeline includes a randomized crossover simulation in which clinicians will manage deidentified cases under 2 conditions: usual care and CDS-assisted care. This simulation will occur after the development and validation phases are complete. Following the simulation, a pragmatic pilot will be conducted in real-world hepatology clinics, where the CDS tool will be integrated into the EHR and used during routine visits. Clinician usability and trust assessments will be administered at the end of each simulation period and again after the pilot phase.

The overall duration of participation for patients in the observational component is expected to be up to 24 months. Clinicians participating in the implementation evaluation will engage in shorter, structured sessions for simulation and a limited rollout period for the pilot.

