### AI Model Development and Validation

The predictive model will be developed using a prespecified machine learning pipeline. Candidate predictors will include longitudinal biochemical markers, platelet count, LSM, SSM, symptom scores, treatment response status, and relevant comorbidities. Features will be selected based on clinical relevance, data availability, and model stability, with highly collinear or sparsely available variables excluded or combined where appropriate.

The dataset will be divided into training, internal validation, and held-out testing subsets at the patient level to avoid data leakage. Model development will use gradient-boosted ensemble algorithms, with hyperparameters tuned within the training set using cross-validation. External validation will be performed using data from at least one participating site not used during model training where feasible.

Class imbalance will be addressed using strategies applied only within the training data, including class weighting or resampling approaches as appropriate. SHAP values will be generated to provide both patient- and cohort-level feature contributions. Model updating will not be performed during initial validation; if performance drift or poor calibration is observed during prospective deployment, recalibration or updating will be conducted using prespecified procedures and reported transparently.

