For the third aim, implementation outcomes will be analyzed using both descriptive and inferential methods. Usability scores from the System Usability Scale (Multimedia Appendix 1), clinician trust scores from the AI trust scale adapted for AIm-PBC (Multimedia Appendix 2), and cognitive load measures from the National Aeronautics and Space Administration Task Load Index (Multimedia Appendix 3) will be summarized and compared between CDS-assisted and usual care conditions. Decision accuracy and decision time will be analyzed using 2-tailed paired *t* tests within the randomized crossover simulation, whereas clinician adherence to guideline-concordant care pathways will be evaluated using within-clinician comparisons across study phases. Feasibility indicators, such as recruitment and completion rates, will be reported as proportions with CIs. Qualitative debriefing interviews will be analyzed to explore clinician perceptions of usability, workflow integration, trust, and barriers to implementation (Multimedia Appendix 4). Fairness metrics, including AUROC parity gaps across demographic and clinical subgroups, will be calculated to ensure equitable performance of the CDS tool.

All analyses will be conducted using validated statistical software packages in R (R Foundation for Statistical Computing) and Python (Python Software Foundation), with significance thresholds set at a 2-sided α value of .05. Missing data will be addressed through multiple imputation techniques, and sensitivity analyses will be performed to confirm the robustness of the findings.

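### Multiple imputation is prescribed for all analyses, including the AUROC of a tool used at clinic visits, and nothing keeps the outcome out of the imputation of held-out patients' inputs

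*Protocol article*

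**What the plan says.** Multiple imputation appears twice in the protocol article. Under Data Collection, directly before the sentence on pipelines that prepare inputs for the machine learning models: "Missing data will be addressed using multiple imputation techniques to minimize bias and preserve statistical power". In the closing paragraph of Statistical Analysis, which governs all analyses: "Missing data will be addressed through multiple imputation techniques, and sensitivity analyses will be performed to confirm the robustness of the findings". No other way of filling or handling missing values is named. For feature selection, AI Model Development and Validation also allows "highly collinear or sparsely available variables excluded or combined where appropriate".

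The same section describes protection against leakage: "The dataset will be divided into training, internal validation, and held-out testing subsets at the patient level to avoid data leakage". Hyperparameters are tuned by cross-validation inside the training set, and "Class imbalance will be addressed using strategies applied only within the training data". It makes no matching statement about imputation.

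Under Outcomes, Aim 2's primary outcome is discrimination measured by AUROC, with calibration, decision curve analysis and net reclassification improvement alongside. Statistical Analysis adds DeLong tests between models. Participant Timeline says of the pragmatic pilot that "the CDS tool will be integrated into the EHR and used during routine visits". Eligibility Criteria require that "baseline elastography data, including LSM and SSM, must be available within 6 months of enrollment". No missing-data rate is given anywhere, and Limitations accepts that bias may remain after imputation.

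**The concern.** Multiple imputation was designed to give valid estimates and standard errors from one incomplete dataset. To avoid diluting associations, the standard form puts the outcome in the imputation model. That is sound for an association model such as those in Aim 1. It is not sound for filling the inputs of patients on whom a prediction model is being tested. Their missing laboratory values or symptom scores would then be drawn with knowledge of whether they had clinically significant portal hypertension (CSPH), and the model would be credited with information it cannot have at a visit.

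A patient-level split does not prevent this by itself. Patients can be kept in separate subsets while each held-out patient's own label still shapes that patient's imputed inputs. The Aim 2 AUROC, its comparison with existing rules, the reclassification figure and the decision curve would all describe a more favourable pipeline than the one clinicians use. Missing inputs are plausible: the plan calls for monthly laboratory tests, twice-daily itch ratings and a monthly questionnaire over up to 24 months.

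**Working it through.** **1. The plan's own figures.** Sample Size and Power Considerations gives about 600 patients and a CSPH prevalence of 24% to 47%. 600 × 0.24 = 144 and 600 × 0.47 = 282, as stated. The AUROC of at least 0.85 in Results is an expectation with no derivation.

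**2. Simulation inputs.** From the article: N = 600, prevalence 24% and 47% (35% as a middle value), complete-data AUROC 0.85. Assumed, because the article gives no figure: a 30% test set; five Gaussian inputs, two standing for liver and spleen stiffness (LSM, SSM); pairwise correlation 0.3 (0 as a variant); values missing completely at random at 10% to 40%; 10 imputations; a linear discriminant score in place of boosted trees; imputation parameters treated as known. There were 60 or 80 repeats per setting.

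**3. Formulas.** The standardised separation is d = √2 × Φ⁻¹(0.85) = 1.414 × 1.036 = 1.466. The mean shift between outcome groups is μ = w·d/√(wᵀΣ⁻¹w). The weights w are 1 for the other three inputs and W for LSM and SSM. For outcome y and prevalence π, missing test inputs were drawn conditionally on the observed ones from:

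- with the outcome: mean yμ, covariance Σ;
- without the outcome: mean πμ, covariance Σ + π(1−π)μμᵀ.

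Training data were imputed with the outcome in both arms, so the difference isolates the handling of test inputs. Excess = test AUROC with the outcome minus test AUROC without it, averaged over imputations.

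**4. Results (excess AUROC).**

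| Setting | 10% | 20% | 30% | 40% |
|---|---|---|---|---|
| Any input may be missing, W = 1.6, prevalence 24% | 0.014 | 0.029 | 0.046 | 0.070 |
| Same, prevalence 47% | 0.014 | 0.029 | 0.046 | 0.068 |
| Any input may be missing, W = 1.0, prevalence 35% | 0.010 | 0.023 | 0.037 | 0.057 |
| LSM and SSM complete, W = 1.6, prevalence 24% or 47% | 0.001 | 0.001 | 0.003 | 0.003 |
| LSM and SSM complete, W = 1.3, prevalence 35% | 0.003 | 0.005 | 0.007 | 0.010 |
| LSM and SSM complete, W = 1.0, prevalence 35% | 0.006 | 0.012 | 0.019 | 0.026 |
| LSM and SSM complete, W = 1.3, correlation 0 | – | 0.022 | – | 0.050 |
| LSM and SSM complete, W = 1.0, correlation 0 | – | 0.032 | – | 0.066 |

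The excess was positive in every setting. In the first row at 30% missing, a score that attains 0.804 without the outcome reports 0.851 with it. If scores are averaged over imputations, the outcome-informed AUROC at 40% missing is 0.880, above the complete-data 0.85.

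**5. Why the elastography-complete rows differ.** At correlation 0.3 the discriminant coefficients are (w − 0.3·Σw/2.2)/0.7. With W = 1.6, Σw = 6.2, so LSM and SSM get (1.6 − 0.845)/0.7 = 1.08 and the other inputs (1 − 0.845)/0.7 = 0.22. The missing inputs then hardly affect the score. With W = 1.0 all five coefficients are equal and the excess rises to 0.026.

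**6. A second simulation.** Chained-equation imputation, data missing at random, prevalence 35% and five equally informative inputs gave an excess of 0.005, 0.010, 0.017 and 0.029 at 10% to 40% missing. With LSM and SSM complete and six weaker inputs missing in 20% to 50%, it gave 0.002 to 0.005. Its benchmark was the score averaged over outcome-free imputations, which is a better score than any single draw. Using that benchmark in the W = 1.0 runs with any input missing gives 0.844 − 0.839 = 0.005, 0.844 − 0.831 = 0.013, 0.850 − 0.831 = 0.019 and 0.848 − 0.817 = 0.031. The two simulations therefore agree closely once the benchmark is the same.

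**The case against.** The strongest reply is that the article states no faulty procedure. It does not say that the outcome enters the imputation model, that imputation is fitted to the whole dataset, or that it precedes the split. Such details often sit in an analysis plan, which is not shown here. The development section speaks of a prespecified pipeline and of avoiding leakage, which points towards proper practice. Sparse variables may be dropped, sensitivity analyses are promised, and the imputation sentences also serve Aim 1, where their rationale fits. All of this stands, and it makes the optimism conditional. It does not remove the point, because the article does prescribe a method for all analyses, and the method's usual form is wrong for held-out inputs.

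The size may also be small. By the Hanley-McNeil formula at AUROC 0.85 and 35% prevalence, the standard error is about 0.018 with 600 patients and 0.033 with 180 (30% of 600). An excess of 0.002 to 0.005 is well inside that. This is fair, although a bias in one direction does not shrink with sample size.

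Three stronger readings are tempting, and the document does not support them:

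- **The reported AUROC will be one the tool cannot reach at a visit.** Use of the outcome is nowhere stated, and for patients with complete inputs the complete-data AUROC is attainable.
- **A single new patient cannot be multiply imputed.** An imputation model fitted in training data without the outcome can be applied to one patient.
- **The bias necessarily favours the composite model over its comparators.** The entry requirement covers baseline elastography only. Follow-up measurements may be missing, and the article does not list the components of the Baveno VII criteria, so it cannot be shown that this comparator needs no imputation.

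**Conclusion.** The point holds as a conditional risk in a stated choice. An inference method is prescribed for a prediction outcome, and the leakage safeguards stop short of it. If held-out inputs were imputed with the outcome, the Aim 2 performance measures would be optimistic for the deployed tool.

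With LSM and SSM complete and predictors correlated at 0.3, the excess AUROC is about 0.001 to 0.026. With uncorrelated predictors it is about 0.02 to 0.07 at 20% to 40% missing. If any input may be missing, it runs from about 0.01 at 10% to about 0.07 at 40%. That last case conflicts with the baseline entry rule, and is relevant only if follow-up elastography enters the model.

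The direction was consistent. The sizes rest on assumed missingness, correlation and split, and on linear scores rather than boosted trees. The change should be made, and confidence in the size is moderate at best.

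**What to change.** Keep multiple imputation for the Aim 1 association models. For Aim 2 and the decision support tool, add a sentence or two to AI Model Development and Validation, for example:

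*Handling of missing inputs is part of the frozen model. It uses either the boosted trees' native treatment of missing values or a single or multiple imputation model fitted in the training data only. The outcome is not used when imputing inputs for held-out or deployment patients. The identical step is applied to test, external-site and pilot patients.*

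Restrict the two existing imputation sentences accordingly. Reporting the missing fraction of each input in the test set would let readers judge how much the handling matters.

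The cost is small, since recruitment and analysis had not begun at submission. The reported AUROC may be slightly lower, but it will describe the tool that clinicians use.

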### AI Model Development and Validation

The predictive model will be developed using a prespecified machine learning pipeline. Candidate predictors will include longitudinal biochemical markers, platelet count, LSM, SSM, symptom scores, treatment response status, and relevant comorbidities. Features will be selected based on clinical relevance, data availability, and model stability, with highly collinear or sparsely available variables excluded or combined where appropriate.

The dataset will be divided into training, internal validation, and held-out testing subsets at the patient level to avoid data leakage. Model development will use gradient-boosted ensemble algorithms, with hyperparameters tuned within the training set using cross-validation. External validation will be performed using data from at least one participating site not used during model training where feasible.

Class imbalance will be addressed using strategies applied only within the training data, including class weighting or resampling approaches as appropriate. SHAP values will be generated to provide both patient- and cohort-level feature contributions. Model updating will not be performed during initial validation; if performance drift or poor calibration is observed during prospective deployment, recalibration or updating will be conducted using prespecified procedures and reported transparently.

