### Sample Size and Power Considerations

Because this protocol involves model development, validation, and implementation feasibility, the planned sample size was based on expected cohort availability and anticipated outcome events rather than a conventional hypothesis-testing formula. The sample size determination for this study is primarily driven by the second aim, which focuses on validating the predictive model for CSPH. On the basis of preliminary data and published estimates, we anticipate enrolling approximately 600 patients with PBC across participating sites [7]. This cohort size reflects the expected availability of retrospective and prospective data within the study time frame and ensures adequate representation of key subgroups, including patients with AIH overlap and MASH [19,20].

On the basis of prior PBC cohorts, the prevalence of portal hypertension or CSPH in hepatology referral populations has been reported to range from approximately 24% to 47% depending on disease stage and case mix [25,26]. With a projected sample of 600 participants, this corresponds to an estimated 144 to 282 CSPH events, which provides a sufficient number of outcome events to support model development and validation and evaluate improvements in model discrimination relative to established criteria such as Baveno VII.

In addition, sample size considerations accounted for model complexity. Current methodological guidance for prediction modeling recommends ensuring an adequate number of outcome events relative to the number of predictor parameters to reduce the risk of model overfitting. The anticipated event counts in this cohort are expected to support the planned set of candidate predictors while maintaining an appropriate events-per-predictor ratio for stable model estimation [27].

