### Statistical Analysis

For the first aim, longitudinal PROs and biochemical markers will be analyzed using mixed-effects models to account for within-subject correlation and repeated measures over time. These models will assess the responsiveness of integrated symptom indexes to changes in biochemical progression or regression, whereas calibration of the AIm-PBC disease activity index will be evaluated against established risk scores such as UK-PBC and GLOBE using the calibration slope, intercept, and Brier score. Discrimination will be quantified through the AUROC, and visualizations of SHAP values will be examined to confirm clinical interpretability.

For the second aim, the predictive model for CSPH complications will be developed using gradient-boosted ensemble algorithms chosen for their robustness in handling heterogeneous data. Model performance will be assessed through the AUROC for discrimination and calibration plots for agreement between predicted and observed outcomes. Clinical utility will be evaluated using decision curve analysis and net reclassification improvement to determine whether the composite model offers meaningful improvement over existing criteria. Comparative analyses will use DeLong tests to assess differences in AUROC between models, and subgroup analyses will be conducted to evaluate fairness and consistency across patients with AIH overlap and MASH. Ablation studies will quantify the incremental value of individual predictors, particularly SSM, by systematically removing variables and observing changes in performance.

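### The three-way data split leaves the Baveno VII comparison and the SSM ablation on a fraction of the events that the sample-size section counts for them

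*Protocol article*

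**What the plan says.** Under AI Model Development and Validation, the protocol article says: "The dataset will be divided into training, internal validation, and held-out testing subsets at the patient level to avoid data leakage". The following sentence specifies gradient-boosted ensembles "with hyperparameters tuned within the training set using cross-validation". The section gives no task to the internal validation subset. External validation is planned at one or more participating sites not used in training, but only if this proves practicable.

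Under Statistical Analysis, for the second aim: "Comparative analyses will use DeLong tests to assess differences in AUROC between models". Ablation studies are to measure the incremental value of predictors, "particularly SSM, by systematically removing variables and observing changes in performance". Neither sentence names the subset on which it is carried out.

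Under Sample Size and Power Considerations, the size is said to be driven mainly by the second aim: "we anticipate enrolling approximately 600 patients with PBC across participating sites". CSPH prevalence "has been reported to range from approximately 24% to 47% depending on disease stage and case mix", and then: "With a projected sample of 600 participants, this corresponds to an estimated 144 to 282 CSPH events". That count is called sufficient "to support model development and validation and evaluate improvements in model discrimination relative to established criteria such as Baveno VII". Nothing is deducted for the split.

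**The concern.** The two sections do not fit together. The sample-size argument counts every event in the cohort for every task. The modelling section divides the patients so that no single task has them all. A comparison on held-out patients sees only the test share, and the model is trained without the patients in the other two subsets.

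The internal validation subset adds to the loss. Tuning has its place in cross-validation and final testing has its place in the test set. As written, the third subset takes patients from both without a stated return.

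At stake are the second aim's primary result (the AUROC), the test against Baveno VII, the estimated contribution of SSM, and the fairness criterion of an AUROC gap of at most 5%. Because the external site is conditional, the internal estimate may be the only evidence on performance.

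**Working it through.** **Inputs from the protocol article.** N = 600 and prevalence 24% to 47% (Sample Size and Power Considerations); expected AUROC 0.85 (Results); two-sided alpha 0.05 (Statistical Analysis).

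**Assumptions not in the document.** Test fraction 15% to 40%; comparator AUROC 0.80; correlation r between the two AUROC estimates 0.5, with 0.3 to 0.7 as a range.

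**Step 1: the plan's own figure.** 600 × 0.24 = 144 and 600 × 0.47 = 282. The stated event range is reproduced exactly. The article gives no power or precision figure to reproduce.

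**Step 2: formulas.** With n1 events and n0 non-events, the Hanley-McNeil standard error is

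SE(A) = sqrt{[A(1−A) + (n1−1)(Q1−A²) + (n0−1)(Q2−A²)] / (n1·n0)}, where Q1 = A/(2−A) and Q2 = 2A²/(1+A).

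For a paired difference, SD = sqrt(s1² + s2² − 2·r·s1·s2). Power = Φ(0.05/SD − 1.96).

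**Step 3: one case in full.** Test fraction 20%, prevalence 24%: n = 120, n1 = 28.8, n0 = 91.2.

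- At A = 0.85: Q1 = 0.7391 and Q2 = 0.7811. The numerator is 0.1275 + 27.8 × 0.0166 + 90.2 × 0.0586 = 5.87, and 5.87/2626.6 = 0.002236. So s1 = 0.0473 and the half-width is 1.96 × 0.0473 = 0.093.
- At A = 0.80, the same formula gives s2 = 0.0528.
- With r = 0.5: SD = sqrt(0.002236 + 0.002785 − 0.002496) = 0.0503. Power = Φ(0.05/0.0503 − 1.96) = Φ(−0.965) = 17%.

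**Step 4: all fractions.** The first value in each cell is at 24% prevalence and the second at 47%.

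| Patients in the estimate | Events | 95% half-width, AUROC 0.85 | Power, 0.85 vs 0.80, r = 0.5 |
|---|---|---|---|
| 90 (15%) | 22 to 42 | 0.107 to 0.082 | 14% to 20% |
| 120 (20%) | 29 to 56 | 0.093 to 0.071 | 17% to 25% |
| 180 (30%) | 43 to 85 | 0.076 to 0.058 | 23% to 35% |
| 240 (40%) | 58 to 113 | 0.065 to 0.050 | 29% to 44% |
| 600 (all) | 144 to 282 | 0.041 to 0.032 | 61% to 82% |

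The difference detectable with 80% power, (1.96 + 0.84) × SD, is about 0.14 to 0.11 with a 20% test set and about 0.06 to 0.05 with all 600.

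**Step 5: sensitivity to r.** Over r = 0.3 to 0.7 and both prevalences, power is 13% to 38% with 120 patients and 47% to 96% with 600.

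**Step 6: how far 600 is a best case.** The bottom row treats out-of-fold predictions as independent scores from one fixed model and ignores refitting variance. An external site would also come out of the same cohort. If that site held 20% of patients (an assumption), 480 would remain. The same formulas then give 115 to 226 events, a half-width of 0.046 to 0.035 and power of 51% to 73%.

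**The case against.** The strongest reply is that the article is silent rather than wrong. A reader might infer that the internal validation subset has no function at all. The document does not show that. It could serve early stopping, a check of calibration after class weighting, or the setting of the dual triage thresholds, and a fuller plan may say so. A reader might equally infer a small random remnant whose result depends on the seed. Neither the size nor random allocation is stated, and because the cohort mixes retrospective and prospective data, a split by time is just as compatible with the text. These objections stand.

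It is also not written that the DeLong tests and ablations use the test set; that is only the natural reading of a held-out testing subset. Nor do the documents support saying that an SSM increment of a few hundredths is indistinguishable from noise. Models with and without SSM share most predictors, so their AUROC estimates should be highly correlated. For an assumed 0.85 against 0.82 with 120 patients, the same formulas give power of 27% to 42% at r = 0.9 and 47% to 68% at r = 0.95, which is weak but not nil. In addition, no test is specified for the ablation.

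The article also says the sample was not derived from a hypothesis-testing formula, so the 0.80 comparator and the 0.05 gain are this review's benchmarks. And a hold-out has a real merit: it tests one frozen model, which suits a tool meant for deployment.

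Two things survive. The mismatch between whole-cohort events and a split cohort does not depend on any of these assumptions. And the merit of testing a frozen model can be kept through an untouched site, without a hold-out from the development data.

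**Conclusion.** The point holds as an inefficient and internally inconsistent use of about 600 patients. It is worth correcting before data collection, but it is not a fatal flaw. For every test fraction from 15% to 40%, the AUROC half-width is no better than about 0.05, the size of the parity gap to be judged, before any subgrouping. At r = 0.5, power for a gain of 0.05 stays below one half. Using all development patients would roughly halve the half-width relative to a 15% to 20% test set.

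These sizes rest on the assumed fractions, comparator and correlation, and on the comparisons using the test set. The figures for 600 patients are an upper bound. The inconsistency itself needs no assumption: the sample-size section counts all 144 to 282 events for a comparison that a held-out test set can make with only some of them.

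**What to change.** In AI Model Development and Validation, replace the three-way split with repeated nested patient-level cross-validation, or bootstrap optimism correction, of the whole pipeline (imputation, feature selection, weighting or resampling, tuning) over all development-site patients. Take the AUROC, the model comparisons and the ablations from this. Use bootstrap confidence intervals that repeat the pipeline, because a plain DeLong test on pooled out-of-fold predictions would ignore refitting. Fit the final model on all development patients and keep at least one untouched site as the test of that frozen model.

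Minimum version, if a hold-out is kept: merge the unassigned internal validation subset into training or test, and restate in Sample Size and Power Considerations the events available for the Baveno VII comparison. This restores consistency but not much power: a merged test set of 240 still gives only 29% to 44% at r = 0.5.

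The cost is about a paragraph of text and more computing, with no extra patients; recruitment had not begun when the article was submitted. The one small downside is that the internal estimate then describes the modelling procedure rather than one frozen model, which is why the untouched site matters.
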